## Abstract

**Background:**

Neglected tropical diseases (NTDs) affect over 1.5 billion people worldwide, the majority of them belonging to impoverished populations in low- and middle-income countries (LMICs). Skin NTDs are a subgroup of NTDs that manifest primarily as skin lesions. The diagnosis and treatment of skin NTDs entail considerable resources, including trained personnel and financial backing. Many interventions are being launched and evaluated, particularly mobile health (mHealth) interventions, such as Skin NTDs App, a training and decision support tool offered by the World Health Organization (WHO) for frontline health workers (FHWs). As most digital health guidelines prioritize the thorough evaluation of mHealth interventions, it is essential to conduct a rigorous and validated assessment of Skin NTDs App.

**Objective:**

We aim to assess the quality of version 3 of Skin NTDs App, developed for the WHO by Universal Doctor and Netherlands Leprosy Relief as a training and decision support tool for FHWs.

**Methods:**

A cross-sectional study will be conducted in 2 LMICs: Ghana and Kenya. We will use snowball sampling recruitment to select 48 participants from the target population of all FHWs dealing with skin NTDs. The sample group of FHWs will be asked to download and use Skin NTDs App for at least 5 days before answering a web-based survey containing demographic variables and the user Mobile App Rating Scale (uMARS) questionnaire. A semistructured interview will then be conducted. Quantitative and qualitative data will be analyzed using SPSS (version 25; SPSS Inc), with statistical significance for all tests set at a 95% CI and *P*≤.05 considered significant. Data derived from the semistructured interviews will be clustered in themes and coded to enable analysis of various dimensions using ATLAS.ti.

**Results:**

The estimated completion date of the study is in the third quarter of 2022. The results are expected to show that Skin NTDs App version 3 has a good reported user experience, as assessed using the uMARS scale. No differences are expected to be found, except for those related to experience in dermatology and the use of mobile technology that could influence the final score. Semistructured interviews are expected to complete the results obtained on the uMARS scale. Moreover, they will be the previous step before assessing other aspects of the app, such as its efficiency and how it should be disseminated or implemented.

**Conclusions:**

This study is the first step in a qualitative and quantitative assessment of Skin NTDs App as a training and support tool for FHWs diagnosing and managing skin NTDs. Our results will serve to improve future versions of the App.

**International Registered Report Identifier (IRRID):**

PRR1-10.2196/39393

## Introduction

Neglected tropical diseases (NTDs) are a group of 20 diseases and conditions identified by the World Health Organization (WHO), which affect over 1.5 billion people. Most of afflicted individuals are women and children living in impoverished populations in tropical and subtropical regions [1]. If not detected or treated, some of these diseases are fatal or can become chronic and irreversible, not only causing lifelong disabilities but also stigma and social exclusion, thereby perpetuating a cycle of poverty with a direct impact on development and economic productivity in low- and middle-income countries (LMICs) [2]. The combination of these factors renders the control of NTDs both necessary and complex.

NTDs had not received global prioritization until 2005, when the WHO established a new strategy to target the group as a whole [1]. Now, NTDs are classified in 2 groups: those that are potentially preventable through large-scale chemotherapy interventions and those that can only be addressed through individual case management [3].

Skin NTDs are a subgroup of NTDs that manifest primarily as lesions on the skin and can be detected through visual screening [4,5]. This group consists of Buruli ulcer, cutaneous leishmaniasis, deep fungal infections, post-kala-azar dermal leishmaniasis, leprosy, lymphatic filariasis, mycetoma, onchocerciasis, scabies and other ectoparasites, and yaws. As most of these conditions do not benefit from large-scale preventive drug administration, they rely on early diagnosis and treatment, which, in turn, relies on considerable resources, including trained personnel and financial backing [4].

Frontline health workers (FHWs) have been identified as vital to the impact of any campaign intended to tackle NTDs [6]. The term FHWs refers to any health worker who directly provides service to a community. As they often have insufficient specialized medical knowledge, data collection procedures, and contact with peers, FHWs need to be equipped with knowledge and tools that will facilitate their role in diagnosing, treating, and referring patients to another level of the health system.

New methods to improve the clinical management and epidemiological surveillance of many diseases, including infectious and skin diseases, have recently been developed [7]. The WHO has recognized that mobile health (mHealth) can be a significant component in delivering global health care and can provide considerable support for FHWs [8]. However, the most recent systematic review of mHealth strategies for dealing with skin NTDs concluded that work is needed to homogenize interventions and thereby reduce methodological limitations [9].

To support FHWs with new technologies, the WHO’s Department of Control of NTDs has developed Skin NTDs App [10], a mobile version of the training guide they published in 2018 [11]. This App helps FHWs diagnose and manage skin NTDs by using an algorithm based on identifying signs and symptoms and provides extra information about these diseases. The recently released version 3, a combination of WHO’s Skin NTDs and SkinApp*,* developed by the nongovernmental organization (NGO) Netherlands Leprosy Relief, has several new features. As yet, the new app is not publicly available, and no evaluations have been conducted. Moreover, studies have shown that relying on the system of “star”-rating iOS and Android devices is insufficient within the exponentially expanding market of medical apps [12].

Most digital health technology frameworks include evaluation of mHealth interventions as a crucial step in ensuring quality and enabling end users to not rely solely on popularity [13-15]. At this point, it is important to emphasize that quality refers to not only clinical effectiveness but also other important domains such as, among others, usability, interoperability, technical security, and data protection [13]. The user version of the Mobile App Rating Scale (uMARS) [12] has been found to be a simple and reliable tool for classifying and rating mobile health apps based on objective and subjective quality domains [14,15].

As the developers of Skin NTDs App have ambitious plans and expectations, it is essential to conduct a rigorous and validated assessment of this app. This paper describes the protocol for a cross-sectional study aimed to assess the engagement, functionality, aesthetics, and quality information for the real end user in their actual context of version 3 of Skin NTDs App in accordance with a validated tool. In addition, a secondary goal of this study will be to determine whether any of the demographic information collected has an impact on the final uMARS score, since the developers of Skin NTDs App do not intend to customize the app when implementing it in any setting.

## Methods

### Study Design

Between April 2022 and May 2022, we will conduct a cross-sectional study among 98 FHWs based in 2 LMICs: Ghana and Kenya.

### Ethics Approval

This study will be conducted in accordance with the ethical principles established by the World Medical Association in the *Declaration of Helsinki–Ethical Principles for Medical Research Involving Human Subjects* [16]. This protocol has been approved by the ethics committee of Universitat Oberta de Catalunya.

Additionally, to ensure that the protocol also meets the ethical requirements in the countries where the study will be conducted, it has been already submitted in Ghana to the Ethical Committee of Kwame Nkrumah University of Science and Technology, Kumasi. The authors have also initiated the process to submit the protocol in Kenya to the Ethical Committee of Coast General Teaching and Referral Hospital, Mombasa.

### Participants and Eligibility

All FHWs who deal with skin NTDs in both selected countries on a daily basis, are responsible for the diagnosis and management of skin NTDs, who own a smartphone device (Apple or Android), and have downloaded Skin NTDs App and used it on at least 5 different days for at least 10 minutes each day are considered eligible. Moreover, participants will need to have access to email or WhatsApp to provide informed consent.

Exclusion criteria are a low comprehension of the English language and refusal to sign the informed consent form.

The target population is the same for both parts of the study. Participants will be asked to read the information sheet (for more detail, see Multimedia Appendix 1) before signing the informed consent form.

### Sample Recruitment

The difficulty of having direct contact with FHWs in these 2 countries necessitates nonprobabilistic snowball sampling, a recruitment technique in which selected participants are asked to identify and contact other potential subjects among their acquaintances to participate in the study. Despite the fact that this method is nonrandomized, it seems to be the most effective way to identify a difficult-to-reach audience, when participants are contacted digitally, and researchers are located in another continent.

The chain of contacts will originate from a medical officer in WHO’s Department of Control of NTDs, who will contact colleagues who work on skin NTDs in the WHO regional and country offices and international NGOs by mail. The country offices will be asked to invite FHWs to participate in the study through Ministries of Health or national NGOs. All FHWs who meet the inclusion criteria and sign the informed consent form will be sent the survey and, if applicable, scheduled for interview (Figure 1).

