### Limitations

There are various limitations associated with this study.

The first limitation that arises and may seem relevant is the decision behind choosing Ghana and Kenya to perform this study. This was based on 3 factors: (1) Skin NTDs App can only be downloaded in English; hence, the choices are limited to countries where English is an official language; (2) these 2 countries have a long history of web-based disease tracking and are endemic for at least 8 skin NTDs each; and (3) to ensure an adequate sampling, countries were chosen on the basis of the accessibility to key officials and program managers and their chances to further contact enough respondents.

Regarding the methodology used, snowball sampling is a nonprobabilistic and nonrandomized method; hence, the sample may not be representative of the general population. However, because the study will be conducted entirely on the internet and the participants and authors are in different places, this is the only way we can connect with FHWs—a highly specialized group that can be challenging to reach in LMICs if contacted remotely.

On the other hand, it is also important to point out some limitations of the uMARS. First, this tool has only been validated among young people using 2 specific apps related to other health areas. However, its high reliability and the inclusion of both objective and subjective domains make it the only questionnaire available that is validated and simple for users to assess health apps.

Another requirement is that FHWs will have to use the app for at least 5 days as opposed to the 10 minutes originally required by the original uMARS publication. Since there will not be any direct control over that, this statement cannot be guaranteed. To determine whether they have fulfilled it or not, a question has been added to the survey.

Finally, it is important to highlight that this study does not claim to assess the clinical effectiveness of Skin NTDs App. This would require a randomized clinical trial and exceed the scope of this study. Although this is version 3, there are still issues to address, including whether information in the app is updated in response to the most recent research.

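### The app's owner starts the invitations, and no eligibility rule or listed survey item screens out or identifies raters tied to the owner or developers

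*Protocol article*

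**What the plan says.** **Who owns the app.** The Introduction states that "the WHO’s Department of Control of NTDs has developed Skin NTDs App". The Abstract's Objective describes version 3 as "developed for the WHO by Universal Doctor and Netherlands Leprosy Relief". The Introduction describes the second app merged into version 3 as "developed by the nongovernmental organization (NGO) Netherlands Leprosy Relief".

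**Who invites the raters.** Under Sample Recruitment, "The chain of contacts will originate from a medical officer in WHO’s Department of Control of NTDs". That officer writes to colleagues in WHO regional and country offices and in international NGOs. Then "The country offices will be asked to invite FHWs to participate in the study through Ministries of Health or national NGOs".

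**Who may rate.** Participants and Eligibility requires smartphone-owning frontline health workers who handle skin NTDs daily, are responsible for diagnosing and managing them, and have used the app on five or more days. "Exclusion criteria are a low comprehension of the English language and refusal to sign the informed consent form".

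**What is recorded.** Demographic Variables calls the survey anonymous and offers three types of working institution: public, private or NGO. The uMARS Questionnaire section adds nine questions and names eight topics for them, including app discovery. None of the named topics is a tie to the WHO or the developers.

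**What is conceded.** Limitations says that "snowball sampling is a nonprobabilistic and nonrandomized method; hence, the sample may not be representative of the general population". It also covers the choice of countries, the validation of the uMARS and the lack of control over app use. It does not discuss the effect of who issues the invitation.

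**The concern.** The main quantitative result is what users say about a product when its owner asks them, through bodies that may be their own authorities. Two mechanisms could raise the scores. Raters with a stake in the app may favour it (affiliation). Raters with no stake may be polite to the body that asked (courtesy).

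Both push towards the result that the article expects, a score above 3 of 5 and a good reported user experience. With one app and no comparator, such a shift cannot be separated from true quality. It would also blunt the candid criticism that the study seeks for later versions.

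Non-representativeness, which Limitations concedes, is a different problem. It concerns who is in the sample, not whether their answers are shifted by who is asking.

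**Working it through.** **Setting the sections side by side**

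| Question | What the article gives | Result |
|---|---|---|
| Does the owner start the chain? | The same WHO department in the Introduction and in Sample Recruitment | Yes |
| Are NGOs a route, and is a developer an NGO? | International and national NGOs in Sample Recruitment; Netherlands Leprosy Relief in the Introduction | Yes to both |
| Are tied raters excluded? | Two exclusions, neither on affiliation | No |
| Can tied raters be identified later? | Public, private or NGO; no named topic on ties | No. NGO mixes a developer's staff with all other NGO staff and misses WHO ties and involvement in testing |
| Does anything reduce the bias? | Survey called anonymous; daily diagnosis and management required | Partly |

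**The plan's own figure.** The Sample Size Calculation takes 100 users and 50% dropout: 100 × (1 − 0.50) = 50. This reproduces the stated 50, which is used below. (The Abstract's 48 and the Study Design's 98 are a separate matter.)

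**Illustration of size.** The article gives no SD, no share of affected raters and no inflation, so all three are assumptions. If a share f of raters scores b points too high, the mean rises by f × b, whatever the sample size.

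- Low case: 0.2 × 0.3 = 0.06 points.
- High case: 0.4 × 0.5 = 0.20 points.
- Standard error with SD 0.6: 0.6/√50 = 0.085.
- Ratios: 0.06/0.085 = 0.7 and 0.20/0.085 = 2.4 standard errors.

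A wider grid (f from 0.10 to 0.50, b from 0.25 to 0.50) gives shifts from 0.10 × 0.25 = 0.025 to 0.50 × 0.50 = 0.25. The 95% half-width at n = 50 is 1.96 × 0.5/√50 = 0.14 with SD 0.5, and 1.96 × 1.0/√50 = 0.28 with SD 1.0. Depending on the assumptions, the shift may be small beside sampling error or may exceed it.

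**When it would change the reading against 3.** A shift of 0.06 moves the expected mean across 3 only if the unbiased mean lies between 2.94 and 3.00. A shift of 0.20 does so only between 2.80 and 3.00.

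**The case against.** The strongest reply is that the design already has safeguards, and that the affiliated rater is hypothetical.

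- **Anonymity.** The survey is described as anonymous, and demographics and uMARS answers are collected in one form. This is a standard counter to deference and it counts. It is not complete: the form is sent by email after signed consent, and it also asks about willingness to be interviewed, so volunteers must be reachable. Anonymity also does nothing about affiliation, and it prevents the tie from being recovered later.
- **Daily care.** A reader might infer that WHO officials or app developers will rate their own product. The documents do not support that. Raters must diagnose and manage skin NTDs daily, and WHO and international NGO colleagues appear as conduits. What remains possible is a field worker of a developer NGO or someone who helped to test the app. Nothing says that such people exist in Ghana or Kenya, and nothing rules them out.
- **The NGO category.** Score differences by working institution are within the stated aims, so scores can be compared by NGO status. That contrast is too coarse to isolate the raters in question.
- **Confidentiality.** A reader might infer that the WHO, ministries or NGOs will see individual ratings, or that raters are not told who will. The text does not say so. The information sheet (Multimedia Appendix 1) is not shown and may cover it, so no fault is found there.
- **Unavoidable features.** A single-app user rating cannot be blinded. The article calls remote snowball contact the only way to reach these workers. The study is at prototype stage and disclaims clinical effectiveness. All of this stands: neither the route nor the lack of blinding is an error.

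**Conclusion.** The point holds as a gap in what the article fixes. The owner starts the invitations, NGOs are both a route and a developer, and neither the exclusions nor the listed items screen out or identify tied raters. The main score is therefore open to a favourable bias that the planned data cannot examine.

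The documents show the risk, not its size. The 0.06 to 0.20 points above are illustrative only. They rest on an assumed share of 20% to 40%, an assumed inflation of 0.3 to 0.5 points and an assumed SD of 0.6, and they combine affiliation with courtesy. They should not be read as an estimate, nor as evidence that the expected result would be false.

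This is a cheap and worthwhile improvement, not a contradiction or a fatal flaw. Its timing matters, because an affiliation not asked for in an anonymous survey cannot be added afterwards.

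**What to change.** 1. Add one yes/no survey item: is the rater employed by the WHO or a developer of the app, or has the rater been involved with them in developing or testing it?
2. Report the uMARS mean score for all raters and again without those who answer yes.
3. Add to Limitations that invitation by the app's owner may bias ratings upward. The item and the restricted score address affiliation only, so this sentence has to carry the courtesy part.

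The recruitment route can stay as it is. The cost is one question and some precision in the restricted analysis. With an assumed SD of 0.6, the 95% half-width is 1.96 × 0.6/√50 = 0.17 for all 50 raters. It stays at about 0.18 if 10% are set aside (1.96 × 0.6/√45) and becomes 0.19 if 20% are (1.96 × 0.6/√40).

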**Figure 1 figure1:**
[figure not shown]
Diagrammatic representation of snowball sampling recruitment. uMARS: user Mobile Application Rating Scale; WHO: World Health Organization.

### Sample Size Calculation

Sample size was calculated on the basis of the 6 stages of the intervention maturity life cycle described by the WHO in *Monitoring and Evaluating Digital Health Interventions* [17], a schematic and practical guide to know which have to be the goals in each stage, how many participants are required, and which are the measurement targets.

Skin NTDs App is currently in the prototype phase, which corresponds to stages 1 and 2 of the 6 stages of the intervention maturity life cycle, according to WHO guidelines. As a result, the WHO advises testing it with a sample size of between 10 and 100 users.

Taking into account that 100 is the maximum recommended number of participants and the web-based modality of this study, we assume a dropout rate of 50%. These calculations leave a final sample size of 50 participants.

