#### Semistructured Interviews

Semistructured interviews are a validated qualitative method for exploring the perspectives, perceptions, and opinions of participants. Semistructured interviews combine prepared questions with others that arise during the interview [18].

In this study, interviewers will ask 8 questions in the same order and using the same words to each participant—a standardization that will facilitate comparability [19]. Questions will be open-ended, neutral, clear, and in familiar language. The structure of the interviews will be as follows: a brief presentation of the interviewer and the study, a general question related to the overall use of Skin NTDs App, 8 core questions directly relating to information needed for app assessment, and unplanned questions that arise during the interview based on the participants’ answers.

It is estimated that semistructured interviews will be conducted in a minimum of the 10% of the final sample size or until information saturation is reached.

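### The participant number is 48 in the Abstract, 98 in Study Design and 100 falling to 50 in Sample Size Calculation; only the last pair follows from the stated 50% dropout, and neither 48 nor 98 is labelled as enrolled or evaluable

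*Protocol article*

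**What the plan says.** Three places in the protocol article state how many people will take part.

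- **Abstract, Methods:** "We will use snowball sampling recruitment to select 48 participants from the target population of all FHWs dealing with skin NTDs".
- **Methods, Study Design:** "we will conduct a cross-sectional study among 98 FHWs based in 2 LMICs: Ghana and Kenya".
- **Methods, Sample Size Calculation:** the basis is World Health Organization (WHO) guidance for the prototype phase, under which "the WHO advises testing it with a sample size of between 10 and 100 users". The authors take the upper end of that range, 100, and "we assume a dropout rate of 50" percent. The section closes with "These calculations leave a final sample size of 50 participants".

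A fourth place uses the result. Under Semistructured Interviews, "semistructured interviews will be conducted in a minimum of the 10% of the final sample size or until information saturation is reached".

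The text does not say how 48 or 98 was obtained, or how either relates to 100 and 50.

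**The concern.** The article contains one sample size calculation, and it produces 100 and 50. The other two figures do not come from it. They are also not marked as numbers before or after dropout, so a reader cannot place them in the chain.

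The Abstract is the more awkward of the two. It speaks of selecting 48 people and then describes what they will be asked to do: use the app, then answer the survey. Taken literally, 48 is counted before any loss, and the protocol's own dropout rate would halve it. Study Design gives 98 with no status at all.

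At stake are the recruitment target and the number of completed user Mobile App Rating Scale (uMARS) questionnaires behind the main result and the comparisons by demographic variable. Sample Recruitment sends the survey to every eligible, consenting FHW and states no cap, so these three statements are all a reader has to go on for the intended size.

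**Working it through.** **Inputs.** 48 (Abstract); 98 (Study Design); 100, 50% dropout and final 50 (Sample Size Calculation); 10% of the final sample size (Semistructured Interviews).

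**1. The plan's own figure.** Final N = starting N × (1 − dropout) = 100 × (1 − 0.50) = 50. This reproduces exactly.

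**2. The other two figures at the same dropout.**
- 98 as the starting number: 98 × 0.50 = 49, which is neither 48 nor 50.
- 48 as the final number: 48 / 0.50 = 96, which is neither 98 nor 100.
- 48 as the starting number: 48 × 0.50 = 24.

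**3. Dropout implied by each pair, 1 − final/start.**

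| Start | Final | Implied dropout |
|---|---|---|
| 100 | 50 | 50.0% |
| 98 | 48 | 51.0% |
| 98 | 50 | 49.0% |
| 100 | 48 | 52.0% |

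Only the first is exact. The others miss by one or two percentage points, that is, by one or two participants at the final count.

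**4. Interview minimum, 10% of N rounded up.** N = 48 gives 4.8, so 5; N = 49 gives 4.9, so 5; N = 50 gives 5. It moves only at N = 24 (2.4, so 3) or N = 98 (9.8, so 10).

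**5. Size of the effect on the mean score.** The document gives no SD for the uMARS app quality mean score. For scale only, assume 0.6 (range 0.5 to 0.8). The 95% CI half-width is t(0.975, n − 1) × SD / √n.

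| Evaluable n | Half-width at SD 0.6 |
|---|---|
| 24 | 0.25 |
| 48 | 0.174 |
| 49 | 0.172 |
| 50 | 0.171 |
| 98 | 0.12 |

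At n = 50 the half-width runs from 0.14 to 0.23 over the assumed SD range. That spread is far wider than the difference between 48 and 50.

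**The case against.** The best defence is that the numbers nearly agree. If 98 and 100 are both recruitment targets and 48 and 50 are both completers, the discrepancy is two people at each end. Sample Size Calculation states its final number and its source openly, and a size drawn from guidance is defensible for a prototype-stage, largely descriptive study. Most of this stands, and it limits how far the point can be taken. A participant number is still a whole number that should be the same wherever it appears, and nothing in the article explains 48 or 98.

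A reader might infer more than the document supports:

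- **That no two of the figures fit the stated dropout.** They do: 100 and 50 fit exactly.
- **That the evaluable number or the interview minimum is undefined.** Sample Size Calculation names 50 as the final sample size, and the interview rule uses the same term. The minimum is 5 at 48, 49 or 50, and the rule also allows saturation as an alternative.
- **That the study will end with 24 evaluable FHWs.** The Abstract's wording permits this, but the figure 24 appears nowhere. The closeness of 48 to the stated final 50 makes a post-dropout number more likely. Participants and Eligibility also makes app use a condition of eligibility, so it is unclear at which step people count as selected.
- **That the plan is deficient because it gives no precision target.** That is a reviewer's preference. Any such statement would need an SD that the document does not contain.

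**Conclusion.** The inconsistency is real and can be checked from the text: 48, 98 and 100 falling to 50 cannot all belong to one chain at 50% dropout, and two of the figures carry no label.

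Its practical effect is probably small. If 98 or 100 are enrolled and 48 to 50 complete, the half-width changes from about 0.174 to 0.171 at the assumed SD of 0.6, and the interview minimum does not change. It matters only under one of two other readings: 48 is the number enrolled, which leaves 24 at the protocol's own dropout and a half-width of about 0.25, or 98 is the number analysed, which gives about 0.12 and a minimum of 10 interviews. The document excludes neither, but does not favour them.

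This is a reporting inconsistency in a headline figure. It should be corrected, but it is not a flaw that threatens the study.

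**What to change.** Use one enrolled and evaluable pair throughout, following from the stated 50% dropout, and label each figure as enrolled or evaluable. The arithmetic already in Sample Size Calculation gives up to 100 FHWs enrolled and 50 completed uMARS questionnaires expected. The Abstract and Study Design can be brought into line with that pair.

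If 98 and 48 were intended, the sponsor should state where they come from and revise Sample Size Calculation to match, since that pair implies 51.0% dropout (50 of 98 lost) and not 50%.

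The cost is a few words in two or three places. It adds no participants beyond the stated maximum of 100 and leaves the analysis unchanged.
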